## Abstract

**Background:**

Breast cancer patients are at an increased risk of insomnia, which can lead to emotional disorders, reduced quality of life, and potentially higher cancer mortality. Auricular acupuncture (AA) offers a feasible treatment option due to its short procedure time, low technical complexity, and relative safety. However, while preliminary studies suggest potential benefits of AA for treating insomnia, the evidence for the population of breast cancer patients remains insufficient.

**Methods:**

This study employs a multicenter single-blind, randomized, controlled trial. A total of 324 patients will be randomly assigned in a 1:1 ratio to either the AA group (n=162) or the nonspecific AA group (NAA) (n=162). Both groups will undergo a 4-week treatment period, with three daily sessions. Follow-up assessments will be conducted at weeks 8 and 16. The primary outcome is the treatment response rate at week 4, and secondary outcomes include the treatment remission rate, the treatment response rate at weeks 8 and 16, change in Insomnia Severity Index (ISI) score, sleep diary, Generalized Anxiety Disorder-7 (GAD-7), Patient Health Questionnaire-9 (PHQ-9), Quality of Life Questionnaire-Core 30 (QLQ-C30), and emergency medication usage. Data will be collected at baseline (week 0), during the intervention (week 2), post-treatment (week 4), and at follow-up (weeks 8 and 16).

**Discussion:**

This study represents an initial effort to develop a comprehensive standard operating procedure (SOP) that includes graphic and video instructions for auricular point location and manipulation techniques. It also provides online guidance to instruct patients on how to self-administer AA at home. The aim of the study is to evaluate the clinical efficacy and safety of AA in treating insomnia among female patients with non-metastatic breast cancer. The findings will provide new insights into the promotion of AA for managing breast cancer-related insomnia in a home-use setting, a method that has the potential to conserve medical resources and alleviate economic burdens.

**Trial registration:**

https://itmctr.ccebtcm.org.cn/mgt/project/view/-7546531521559384755, identifier ITMCTR2025001101.

## Background

Breast cancer is the most prevalent cancer among women worldwide, accounting for 11.6% of all cancer cases and serving as a leading cause of cancer-related deaths (1). According to the 2022 Global Cancer Statistics, approximately 2.3 million new cases and 665,000 deaths occur annually (1). Insomnia is a prevalent clinical issue among cancer patients, occurring at a rate approximately three times higher than in the general population (2). It can manifest at any stage of cancer and is particularly common in breast cancer patients (3, 4). Insomnia not only heightens the risk of mental and physical comorbidities but also impairs patient adherence to cancer treatments, thereby negatively impacting treatment outcomes (5). Furthermore, sleep quality significantly influences immune function, neuroendocrine function, cognitive health, and overall quality of life (6).

Current interventions for insomnia in breast cancer patients primarily include pharmacotherapy, cognitive behavioral therapy, acupuncture, and Tai Chi. Although numerous studies have demonstrated the effectiveness of these interventions in improving sleep in breast cancer patients, limitations persist (7–9). As such, effective and proactive management of insomnia in this patient population remains a critical challenge in clinical practice.

AA, a non-pharmacological approach, is based on the principle that the auricle corresponds to the body’s internal organs. Specific regions of the auricle are innervated by the auricular branch of the vagus nerve, which is the only cutaneous branch of this nerve and plays a crucial role in regulating various physiological processes in humans (10). By stimulating specific auricular points, the auricular branch of the vagus nerve is activated, which in turn regulates the function it innervates and treats diseases like insomnia (11, 12). In this trial, “auricular acupuncture” refers to the insertion and retention of intradermal needles at specified auricular points, combined with patient self-administered acupressure and home-based needle replacement following the video SOP and operation manual. While preliminary studies have suggested the clinical efficacy of AA for insomnia, limitations remain, particularly among breast cancer patients (13, 14). Existing studies are primarily single-center, small-sample investigations, and there is a lack of well-designed control groups, leading to considerable heterogeneity in the evaluation of treatment outcomes (15).

To address these gaps, we have designed a multicenter, randomized controlled trial to assess the clinical efficacy and safety of AA, compared to NAA, in treating insomnia in breast cancer patients. This study aims to provide robust, evidence-based findings to support the use of AA for female patients with non-metastatic breast cancer, thereby informing clinical treatment strategies.

## Methods

### Study design

This study will be conducted across three centers, including LongHua Hospital, Shanghai University of Traditional Chinese Medicine; Zhongshan Hospital, Fudan University; and Huashan Hospital, Fudan University. A total of 324 patients will be recruited and randomly assigned in a 1:1 ratio to either the AA group or the NAA group. Both groups will undergo a 4-week treatment, followed by a 12-week follow-up. **Figure 1** illustrates the flowchart of the trial, and **Table 1** presents a schematic timeline outlining the recruitment process, intervention schedule, and efficacy evaluations. The protocol for this study was based on the Standard Protocol Items: Recommendations for Intervention Trials (SPIRIT) 2013, as outlined in **Supplementary Material 1**.

**Figure 1 f1:**
[figure not shown]
Trial flow chart. ISI, Insomnia Severity Index; GAD-7, Generalized Anxiety Disorder Scale-7; PHQ-9, Patient HealthQuestionnaire-9; QLQ-C30, Quality of Life Core Scale-30.

**Table 1 T1:** Schedule of enrolment, interventions and assessment times.

Study period	Enrolment		Intervention period				Follow-up period	
Time point	Week -1	Week 0	Week 1	Week 2	Week 3	Week 4	Week 8	Week 16
Eligibility screen	**×**							
Sign informed consent	**×**							
randomization		**×**						
Interventions								
Auricular acupuncture								
Nonspecific auricular acupuncture								
Primary outcomes								
Treatment response rate						**×**		
Secondary outcomes								
Treatment remission rate				**×**		**×**	**×**	**×**
Treatment response rate				**×**			**×**	**×**
Change in ISI score				**×**		**×**	**×**	**×**
Sleep diary								
GAD-7		**×**				**×**		
PHQ-9		**×**				**×**		
QLQ-C30		**×**				**×**		
Adverse events			**×**	**×**	**×**	**×**		
Emergency medication usage			**×**	**×**	**×**	**×**	**×**	**×**
Success of blinding						**×**		

### Patients

Recruitment will be conducted through the hospital’s official online platform and posters. Patients who meet the inclusion criteria will be invited for a face-to-face interview and baseline assessment. Before signing the informed consent form (ICF), all patients will be thoroughly briefed on the potential benefits, risks, and study requirements through both verbal explanations and written materials. Eligible patients will then be randomly assigned to either the AA or the NAA group. Patients may withdraw from the study at any time.

### Inclusion criteria

(1) Participants are required to have stage I-III breast cancer, diagnosed and staged according to the NCCN Clinical Practice Guidelines (2022, 2nd ed.) and the AJCC Cancer Staging Manual (8th ed.), respectively. Insomnia will be assessed with reference to Diagnostic and Statistical Manual of Mental Disorders, 5th Edition (DSM-5), with symptoms occurring at least three nights per week for ≥1 month after breast cancer diagnosis and related to the malignancy or its treatment. (2) Female patients aged between 18 and 75 years. (3) Eastern Cooperative Oncology Group (ECOG) performance status score of ≤2. (4) ISI score of ≥8. (5) An estimated survival period of ≥6 months. (6) Written ICF to participate in the study.

### Exclusion criteria

(1) Those with severe heart, liver, kidney or other major diseases; (2) Those who are pregnant, lactating or planning to become pregnant within the next month; (3) Those with surgical plans during the trial period; (4) Those with a history of drug abuse or addiction; (5) Those who have taken sedative-hypnotic or antipsychotic drugs within two weeks before baseline, or have received other insomnia treatments (such as cognitive behavioral therapy, etc.) within three months before baseline; (6) Those with insomnia caused by cancer pain (NRS score≥4) or other physical diseases; (7) Those with mental or intellectual abnormalities who cannot finish the assessment; (8) Those who have long-term night work or irregular schedules; (9) Those who have received AA treatment within three months prior to enrollment; (10) Those with ulcers, abscesses, skin infections or other conditions at the treatment sites; (11) Those allergic to metals and adhesive tapes; (12) Those with ear deformities, perforations, cartilage deformations or other conditions; (13) Those with auricular cartilage inflammation or other serious complications related to the ear; (14) Those who have participated in other clinical medical trials within the past month.

### Randomization, allocation concealment and blinding

The random allocation scheme for this study will be generated by researchers at the Clinical Research Center of LongHua Hospital, Shanghai University of Traditional Chinese Medicine, who will not be involved in participant recruitment, intervention delivery, outcome assessment, or statistical analysis. A block randomization method will be employed, with allocation codes in opaque envelopes provided by the data management center. Patients will be informed that they have an equal chance of being assigned to either the AA group or the NAA group. Moreover, strict adherence to the principle of departmental separation will be enforced to ensure the reliability and validity of the research.

A single-blind research design will be adopted, whereby all patients, evaluators, and statistical analysts, except for the acupuncturists, will remain unaware of group allocations. To facilitate successful blinding, all researchers will undergo rigorous training on the standardized implementation of the research protocol for two groups, including standardized communication, similar external appearance of the adhesive devices and procedural instructions, separation of appointment times to reduce communication between participants, restriction of communication regarding group allocation, and separation of acupuncturists from outcome assessment and data analysis. Outcome assessors will remain blinded throughout the trial and will not participate in intervention delivery. After the 4-week intervention, participants will be asked to guess group allocation as “AA”, “NAA” or “uncertain” and blinding integrity will be evaluated using the Bang Blinding Index. Unblinding will be permitted only when required for participant safety or trial management, and all unblinding events will be documented.

### Intervention

Throughout the study, all patients will receive the same standardized sleep hygiene education, which includes guidance on avoiding caffeine, tea, alcohol, and other stimulating beverages, maintaining regular daily schedules and appropriate sleep environments, and managing emotional well-being. Patients will be required to maintain a sleep diary for five weeks, documenting their sleep patterns at the following time points: week 0 - week 4.

All acupuncturists from the three centers will receive centralized standardized training before trial initiation, covering auricular point location, device application, insertion depth, disinfection procedures, patient instruction, and adverse event identification. Regular cross-center quality control meetings will be conducted to ensure protocol consistency.

Before home-based self-administration, participants will receive standardized training from trained acupuncturists, including face-to-face demonstration, video SOP instruction, and written operation manuals (**Supplementary Material 2**). During the first and fifth treatments, acupuncturists will verify participants’ ability to correctly locate auricular points, disinfect the auricle, apply the device, and perform pressing stimulation. During home treatment, participants will record device replacement and daily stimulation, upload operation photographs or videos weekly for researcher verification, and complete electronic adherence check-ins through WeChat. If incorrect operation or poor adherence is identified, researchers will provide timely guidance and retraining. A contact number will be provided for reporting adverse events (AEs) or operational problems.

If a patient experiences severe insomnia-related discomfort for two consecutive days or more, emergency medication usage may be used based on clinical need. The use of rescue medication is intended for short-term symptomatic relief and is not encouraged as routine treatment. Researchers will carefully record the name, dosage, frequency, and duration of medication use in the Case Report Form (CRF).

### Auricular acupuncture group

Patients in AA group will receive treatment at five auricular acupoints: subcortex (AT_4_), heart (CO_15_), shenmen (TF_4_), liver (CO_12_), and sympathetic nerve (AH_6a_) (11) (**Figure 2**; **Table 2**). Sterile AA devices (0.20*1.5mm) from SEIRIN CORPORATION (Japan) will be used. Prior to treatment, the auricular acupoints will be disinfected using 75% alcohol. The acupuncture devices will be inserted to a depth of 1.5mm and secured with adhesive tape. Each acupoint will be manually stimulated by finger pressure for 30 seconds or until the auricle turns red, with stimulation occurring three times daily (11, 16). The AA devices will be replaced twice a week (every three days), alternating between the left and right auricular acupoints. This process will entail a total of eight applications over a 4-week period, followed by a 12-week follow-up (**Figure 3**). The first and fifth treatments will be administered by a trained acupuncturist.

**Figure 2 f2:**
[figure not shown]
The locations of auricular acupoints in both the AA and NAA groups.

**Table 2 T2:** The locations of auricular acupoints in both the AA and NAA groups.

Group	Auricular acupoint	Location
Auricular acupuncture group (AA)	Sympathetic nerve (AH_6 a_)	At the junction of the anterior end of the inferior crus of the antihelix and the inner margin of the helix, which corresponds to the anterior end of the sixth region of the antihelix.
	Heart (CO_15_)	In the central depression of the concha, specifically in the 15th area of the concha.
	Shenmen (TF_4_)	In the upper part of the posterior one-third of the triangular fossa, specifically in area 4 of the triangular fossa.
	Liver (CO_12_)	In the posterior inferior part of the concha, specifically in the 12th region of the concha.
	Subcortex (AT_4_)	On the medial side of the antitragus, specifically in the 4th region of the antitragus.
Nonspecific auricular acupuncture group (NAA)	External ear (TG_1 u_)	In front of the incisura on the screen, near the helix, that is, at the upper edge of the tragus area 1.
	Lunyi (HX_9_)	At the helix below the helix tubercle, which is helix region 9.
	Luner (HX_10_)	At the helix below wheel 1, which is helix region 10.
	Lunsan (HX_11_)	At the helix below wheel 2, which is helix region 11.
	Lunsi (HX_12_)	At the helix below wheel 3, which is helix region 12.

**Figure 3 f3:**
[figure not shown]
Treatment flow chart.

### Nonspecific auricular acupuncture group

In the NAA group, External ear (TG_1u_), Lunyi (HX_9_), Luner (HX_10_), Lunsan (HX_11_), Lunsi (HX_12_) will be used (11). Sterile AA devices (specifications: 0.20*0.3mm) from SEIRIN CORPORATION (Japan) will be employed, with needles being inserted to a depth of 0.3mm. It is important to note that the retention time and replacement method for the AA devices in the NAA group will follow the same protocol as that of the AA group.

### Outcomes

#### Primary outcome

The primary outcome is the treatment response rate, defined as the percentage of patients whose total ISI score decreases by ≥8 points compared to the baseline score at the end of the 4-week treatment period (17, 18).

The ISI is a reliable and valid self-report tool used to measure insomnia. It assesses aspects such as difficulty falling asleep, staying asleep, waking up early, sleep satisfaction, daytime impairment, and overall quality of life. The ISI uses a 7-item scoring system, with total scores ranging from 0 to 28, where higher scores indicate more severe insomnia. According to clinical criteria, scores of 0–7 indicate no significant insomnia, 8–14 indicate subthreshold insomnia, 15–21 indicate moderate insomnia, and 22–28 indicate severe insomnia.

#### Secondary outcome

The secondary outcomes include the following eight indicators:

Treatment remission rate: The percentage of patients achieving an ISI score <8 at weeks 2, 4, 8, and 16.Treatment response rate at weeks 2, 8, and 16.Sleep diary (19): Total sleep time (TST), sleep onset latency (SOL), number of sleep awakenings (SA), wake after sleep onset (WASO), early morning awakenings (EMA), average duration of awakenings (ADA), and sleep efficiency (SE), as recorded in sleep diaries at weeks 0, 1, 2, 3, and 4.Change in ISI score: This will be evaluated at weeks 2, 4, 8, and 16.Generalized Anxiety Disorder-7 (GAD-7) (20): This scale assesses anxiety symptoms experienced by patients in the past two weeks. Evaluations will be conducted at Weeks 0 and 4.Patient Health Questionnaire-9 (PHQ-9) (21): This scale evaluates depression symptoms in the past two weeks. Evaluations will take place at Weeks 0 and 4.Quality of Life Questionnaire-Core 30 (QLQ-C30) (22): This 30-item scale assesses the quality of life among cancer patients across six dimensions and is widely used in clinical research. Assessment will be conducted at Weeks 0 and 4.Emergency medication usage: The percentage of patients using emergency medication usage, as well as the dosage, frequency, and duration of medication use, will be recorded at weeks 1, 2, 3, 4, 8, and 16.

#### Adverse events

AEs associated with AA may include redness at the needle site, ear swelling, fainting due to the needle, local infections, and exacerbation of symptoms due to excessive stimulation. The severity of these AEs and causality between AEs and the intervention will be assessed by researchers and recorded in detail in the CRF. In the event of serious AEs, researchers will promptly report them to the ethics committee and will determine whether to suspend or withdraw the trial. The incidence of AEs will be calculated as the percentage of patients experiencing AEs during the trial. The intervention may be discontinued if participants request withdrawal, experience serious adverse events, or are judged unsuitable for continued treatment by investigators.

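### Adverse events are scheduled for assessment only in weeks 1 to 4, but their incidence is defined over the whole trial, so events in follow-up rest on spontaneous report

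*Protocol article*

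**What the plan says.** The Adverse events section of the protocol article fixes the safety measure: "The incidence of AEs will be calculated as the percentage of patients experiencing AEs during the trial". It gives no range of weeks. The Study design section sets the length of participation: "Both groups will undergo a 4-week treatment, followed by a 12-week follow-up". The Auricular acupuncture group section describes the same course: "This process will entail a total of eight applications over a 4-week period, followed by a 12-week follow-up".

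In Table 1 the row labelled "Adverse events" has marks at weeks 1, 2, 3 and 4 and none at weeks 8 and 16. The next row, emergency medication usage, does carry marks at weeks 8 and 16, and the Secondary outcome section confirms that this item "will be recorded at weeks 1, 2, 3, 4, 8, and 16".

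The reactions that the plan expects include "redness at the needle site, ear swelling, fainting due to the needle, local infections, and exacerbation of symptoms". Outside the schedule, the Intervention section offers one further route: "A contact number will be provided for reporting adverse events (AEs) or operational problems". It states no end date for that route. The Statistical analysis section names a Safety Set and compares adverse-event incidence between the groups with chi-square or Fisher's exact tests.

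**The concern.** The numerator of the safety measure and the schedule that fills it cover different periods. If both are followed as written, one percentage combines two kinds of ascertainment: planned checks in weeks 1 to 4, and whatever patients volunteer from then to week 16. Spontaneous report generally picks up less than asking, so a figure labelled as trial-wide would in practice be close to a treatment-period figure.

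This matters because safety is a stated aim alongside efficacy. The devices penetrate the skin, an acupuncturist applies only the first and fifth of eight applications, and the patient replaces the others at home. The Discussion itself names adverse-event monitoring as a challenge of the home-based model. Local infection is on the protocol's own list and can appear after a device has been removed.

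**Working it through.** The article gives no adverse-event rate and no figure to reproduce on this point. The check sets the sections side by side, with simple arithmetic on the windows.

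**1. Is the empty cell real?** The text comes from a PDF, so a lost mark is possible in principle. The adverse-event row has its own four marks, and the emergency medication row directly below keeps its marks at weeks 8 and 16. The Secondary outcome text confirms those weeks for medication. No sentence in the article places an adverse-event assessment after week 4. The row is best read as intact.

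**2. Coverage.** Inputs: 4 weeks of treatment and 12 weeks of follow-up (Study design); assessments at weeks 1 to 4 (Table 1).
- Participation: 4 + 12 = 16 weeks.
- Scheduled adverse-event collection: 4/16 = 25%.
- No scheduled collection: 12/16 = 75%, including both follow-up contacts.

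The 16 weeks are inferred. The incidence definition names the trial, not a number of weeks.

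**3. When does the last device come off?** The article gives no removal day. It describes replacement both as twice weekly and as every three days, with eight applications.
- Strict three-day interval: 8 × 3 = 24 days of wear, so removal at about day 24 to 25.
- Twice-weekly calendar (days 1, 4, 8, 11, 15, 18, 22, 25): removal at about day 28.

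If the week 4 assessment falls on day 28 (an assumption), scheduled observation after the last removal lasts between about 0 and 3 or 4 days. The Abstract calls the week 4 data collection post-treatment, so some observation after removal may be intended.

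**4. How many events could fall in the unscheduled window?** The documents give no late-onset risk. For an assumed risk q per patient in weeks 5 to 16, the expected number per group is 162 × q:

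| Assumed q | Patients per group of 162 |
|---|---|
| 0.5% | 0.8 |
| 1% | 1.6 |
| 2% | 3.2 |
| 5% | 8.1 |

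These are patients with an event in that window, not patients whose event goes unrecorded. Some would report it.

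**5. Effect on the comparison.** The gap is the same in both groups by schedule, but its effect need not be. Insertion depth is 1.5 mm in the AA group and 0.3 mm in the NAA group. If late local reactions depend on depth, the gap would hide more of them in the AA group and make the groups look more alike. The direction is plausible, but the article has no figure to size it.

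**The case against.** The case for leaving the plan alone has several parts.

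- **Late events are not shut out.** A reader might infer that everything after week 4 is lost. The article does not support that. The contact number has no stated end date, recording in the case report form and prompt reporting of serious events carry no week limit, and patients are seen again at weeks 8 and 16. What stands is that late events depend on spontaneous report.
- **The last application may be observed after removal.** A reader might infer that the eighth device is worn to the end of week 4, so that no check follows its removal and one eighth of exposure goes unobserved. No section gives the removal day, and the three-day interval would leave a few days before day 28. That inference cannot be used.
- **Twelve weeks sounds larger than it is.** No device is worn in follow-up, and most listed reactions are immediate or device-related. The relevant period is mainly a short tail after the last removal. This stands and limits the size of the problem.
- **Collecting adverse events only during treatment is a legitimate choice.** It is, but the incidence definition would then have to say so.
- **A condensed article leaves exact windows to the full protocol.** That would excuse silence. Here the article states both the schedule and the definition, and they disagree.

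**Conclusion.** The mismatch holds. Adverse events are scheduled for assessment at weeks 1 to 4, their incidence is defined over the trial, and nothing in the article reconciles the two. As written, the reported percentage would not correspond to its definition and could understate delayed local events, chiefly infection after the last self-applied devices.

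The size cannot be derived from the article and is probably small. The conclusion assumes that the trial includes the 12-week follow-up, which is the natural reading of Study design, and that the Table 1 row is complete as printed. The primary outcome, the sample size and the efficacy analyses are untouched. The point deserves correction because safety is a stated aim and the remedy is cheap.

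**What to change.** Preferred: add adverse-event marks at weeks 8 and 16 in Table 1, and ask about events since the last contact at those two assessments, which already take place for the ISI outcomes and emergency medication. State the window as first application to week 16. In the Safety Set, report the on-treatment incidence (weeks 1 to 4) separately from the whole-trial incidence.

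Minimum: restate the incidence in the Adverse events section as treatment-period only, so that it agrees with Table 1, and say how late-onset or ongoing events are followed and reported.

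The preferred change costs one question at two existing contacts and a table amendment. Its small downside is that some events unrelated to the devices will be recorded. The minimum change costs two sentences and adds no data collection, but it leaves late events to spontaneous report. Recruitment is described as still to start, so either can be made before enrolment if that remains the case.
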